##### Feasibility

The feasibility of recruitment will be measured by the percentage of the sample size that is recruited. To measure the retention rate of participants, the attendance of the participants in the intervention training sessions and their level of compliance with intervention guidelines will be recorded. Furthermore, facilitators and participants in the intervention will be asked questions about the feasibility of scaling the intervention and conducting a similar but larger-scale trial in both the survey questionnaires and in-depth interviews that will be administered at the end of intervention delivery.

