#### Aim 3: Pilot Trial of the Intervention Packages

##### Overview

The aim of this phase of the project is to pilot the coproduced intervention packages developed in phase 2 of the project to assess their feasibility, acceptability, cost, and potential effectiveness. This phase will also assess the factors that facilitated and hindered the implementation of the piloted intervention packages and what needs to be learned before scaling up.

The pilot of the ARISE&WIN interventions has been planned as a quasi-experimental study with a prepost design. The design was chosen because there was unanimity around it being feasible while allowing us to draw conclusions about the potential effectiveness of various interventions. The study will consist of 3 arms. One of the intervention groups will receive the capacity building intervention package. The second intervention group will receive the social protection intervention package in addition to the capacity building intervention package. The capacity building and the social protection interventions will be finalized during the coproduction process. The third group will be a control group serving as a comparison group, and participants will not receive any intervention. The pilot will be conducted in the LGAs of Greater Ibadan, where situational analysis has been conducted. The LGAs will be stratified into urban, periurban, and rural LGAs and randomly assigned to 1 of the 2 intervention groups or the control group. On the basis of recommendations from literature [43,44] on pilot trials, a sample size of 120 participants would be large enough to assess feasibility and other outcomes of interest in the pilot study. To account for possible attrition, the sample size would be rounded up to 150 in total, with 50 participants per arm of the trial. Frequency matching will be conducted to ensure that across the intervention and control LGAs, the participants will have similar characteristics based on age and their sector of occupation. Participants will be recruited through advertisements on social media platforms where self-employed young women are active. Announcements will also be made at business association meetings to identify eligible participants. Participants will also be recruited through partner organizations (SMEDAN and the Centre for Support of Women in Unpaid and Informal Employment in Nigeria) that work with self-employed young women.

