All groups will participate in a preintervention survey. Then, the interventions will be delivered over a period of 4 months. Follow-up surveys will be conducted at 6 weeks at the end of the capacity building intervention and months 4, 6, and 12. As part of a process evaluation, in-depth exit interviews will be conducted with approximately 20 participants to gain deeper insights into their perceptions about the interventions they receive. In addition, a survey will be administered to intervention facilitators while a subset of them will participate in in-depth interviews.

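### The stated retention measure is adherence to the intervention: it is undefined for the control arm and does not measure loss to follow-up

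*Protocol article*

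**What the plan says.** All references are to the protocol article, Aim 3 (pilot trial of the intervention packages).

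- **Feasibility** names what will be recorded for retention: "To measure the retention rate of participants, the attendance of the participants in the intervention training sessions". The same sentence adds, as a second component, how far participants comply with the guidelines of the intervention. The article gives no other measure of retention.
- **Overview**, on the control arm: "The third group will be a control group serving as a comparison group, and participants will not receive any intervention".
- **Overview**, on sample size, gives 120 as sufficient for a pilot and then enlarges it: "To account for possible attrition, the sample size would be rounded up to 150 in total". That is 50 per arm. No attrition rate is given.
- **Overview**, on timing, has every group surveyed at baseline and a delivery period of 4 months. The later schedule reads: "Follow-up surveys will be conducted at 6 weeks at the end of the capacity building intervention and months 4, 6, and 12".
- **Analysis** compares study outcomes across the three groups, so outcome data are expected from the control arm as well.

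**The concern.** Retention in a trial is the share of enrolled participants who still provide outcome data at a given time. Attendance and compliance describe something else, namely how far a participant took up what her arm was offered. The two can part company: a woman may miss sessions and complete every survey, or attend every session and be lost by month 12.

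The mismatch matters here for three reasons.

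- One of the three arms has no sessions to attend and no guidelines to follow.
- Half of the follow-up surveys fall after delivery has ended.
- The sample was enlarged for attrition across all three arms, but the measure cannot say how much attrition occurred in all three.

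Feasibility is a named aim of the pilot, and the Discussion describes the pilot as preparation for a large-scale efficacy trial. Loss that differs between an untreated control arm and two treated arms is an obvious threat to the three-group comparison. A retention figure built on attendance would be silent about it.

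**Working it through.** **1. The plan's own figure.** The Overview gives 120 before and 150 after the attrition allowance, with 50 per arm: 3 × 50 = 150, which is consistent. The rate behind it is not stated and can only be back-solved:

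- With n/(1 − d): 120/(1 − 0.20) = 150, so d = 1 − 120/150 = 20%.
- With n × (1 + d): 120 × 1.25 = 150, so d = 25%.

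Both describe the same step from 120 to 150. If 120 is the number to be retained, the tolerated loss is 30 of 150, or 20%. That reading is an assumption.

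**2. Who has a value.** Attendance and compliance exist for the two intervention arms only: 2 × 50 = 100 of 150. The control arm, 50/150 = 33%, has none. The one-third share holds for any total with equal arms.

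**3. Which time points attendance can reach.** Delivery lasts 4 months. The follow-up surveys are at 6 weeks and months 4, 6 and 12. Months 6 and 12, two of the four, come after delivery, when no session attendance can be recorded in either intervention arm.

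**4. What an intervention-only measure would hide.** This illustration uses assumed values. Suppose 80 of the 100 intervention women are retained and, generously, that the stated measure captures this correctly. It then reads 80% whatever happens in the control arm. True overall retention is (80 + c)/150, where c is the number of control women retained:

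| Control retained (c) | Control retention | True overall retention | Stated measure |
|---|---|---|---|
| 50/50 | 100% | 130/150 = 86.7% | 80% |
| 45/50 | 90% | 125/150 = 83.3% | 80% |
| 40/50 | 80% | 120/150 = 80.0% | 80% |
| 35/50 | 70% | 115/150 = 76.7% | 80% |
| 30/50 | 60% | 110/150 = 73.3% | 80% |
| 25/50 | 50% | 105/150 = 70.0% | 80% |

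The reading stays at 80% while the difference between control and intervention arms runs from +20 to −30 percentage points.

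**5. What survey completion would give.** Assuming 80% completion, the Wilson 95% interval is 67.0% to 88.8% per arm (40/50) and 72.9% to 85.6% overall (120/150). These intervals show the precision available and do not measure the size of the fault. They treat women as independent, although arms are assigned by local government area, so they may be too narrow. They also use the Overview's total of 150. The abstract says 300, a separate discrepancy; with 300 in equal arms the intervals would be about 71% to 87% per arm and 75% to 84% overall.

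**The case against.** The strongest reply is that the data will exist. All groups take the baseline survey, the follow-up schedule is not limited to the intervention arms, and the analysis compares three groups. Survey completion by arm can therefore be counted at every visit. This stands. A reader might infer that the pilot is unable to detect attrition or differential loss, and the documents do not support that. They support only that the measure the article names would not report it.

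A second reply is that retention may here mean staying in the training programme, which is a legitimate feasibility item for a pilot of intervention packages, and that a condensed article may leave denominators and follow-up accounting to a fuller document. Part of this stands: the sentence gives no formula and does not say that nothing else will be counted. But the article does not leave the matter open. It names a measure for the retention rate of participants, and that measure does not fit. If programme retention is meant, the label should say so, and the article then states no measure of study retention although it enlarges the sample for attrition.

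Two further inferences go too far. One is that the plan budgets for 20% attrition: it states no rate. The other is that in the arm receiving capacity building alone the measure covers only the first 6 weeks of 12 months. The article does place the end of capacity building at 6 weeks, but compliance with guidelines is the other half of the measure and need not stop when sessions stop. The safer statement is that attendance cannot reach months 6 and 12.

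**Conclusion.** The point holds as a badly chosen definition in the stated text. Following that text gives no retention value for the control arm (one third of participants if arms are equal, 50 of 150 on the Overview's figures), and its attendance component cannot bear on two of the four follow-up surveys. The resulting figure would describe adherence in the intervention arms. It would leave loss to follow-up, differential loss and the allowance from 120 to 150 unreported.

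The harm is limited because survey completion can be recovered from the planned data, and no outcome analysis depends on the definition. It is worth correcting because it affects a headline feasibility result. The one-third figure assumes equal arms. The implied 20% and the 80% used in the illustrations are assumptions.

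**What to change.** In the Feasibility section:

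- Define retention as the proportion of enrolled women who complete each follow-up survey (6 weeks, months 4, 6 and 12), with all enrolled women in each arm as the denominator, reported by arm with 95% confidence intervals.
- Report session attendance and compliance with guidelines separately, labelled as adherence, for the two intervention arms only.
- If retention is to be compared with the attrition allowance, state the rate assumed in going from 120 to 150, so that the comparison is with the plan's own figure and not one inferred from it.

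The cost is a change of wording and one additional table. The surveys are already scheduled, so no new data collection is needed, and the change can be made while the pilot is under way.

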##### Acceptability

To assess the acceptability of the interventions to the participants, they will be asked about how helpful they found the intervention, whether they liked the way the intervention was delivered, and their thoughts about the data collection instruments and the frequency of administration. The acceptability of the RCT design will also be assessed.

##### Cost

Comprehensive records of all costs incurred in implementing the intervention will be kept, including the costs of recruiting the participants and other intervention implementation costs, such as facilitator and participant compensation, training materials, equipment and venue renting, catering costs, transportation, and childcare costs of the participants. This will be used to calculate total costs as well as per-unit costs for participants.

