### Ethical Considerations

The project will follow international research standards and be guided by the Principles for Global Health Research by the Canadian Coalition for Global Health Research. Ethics approval has been obtained from the Oyo State Ministry of Health Research Ethics Committee (reference number: NHREC/OYOSHRIEC/10/11/22), University of Ibadan and University College Hospital Ethics Committee (reference numbers: UI/EC/23/0256 and UI/EC/24/0809), and McGill University Ethics Committee (reference number: A11-B42-23A). Written informed consent or assent will be obtained from all participants before their enrollment into the study. Participants aged <18 years will be required to provide assent, while informed consent will be obtained from their parents. No names or any other forms of identification will be used in publications or reports resulting from the study without the permission of the participants. In keeping with recommendations for digital storytelling, participants will have the choice of identifying themselves and sharing their testimony. The consent and assent forms, interview guides, and questionnaires have been translated to Yoruba, the local language of the study location, using World Health Organization–recommended translation and back-translation procedures. This has been done to ensure that participants understand the study procedure fully and make an informed decision about whether to participate or not. Participants will be compensated monetarily for their time participating in this study as well as their transportation costs. This compensation will range from 2000 Nigerian naira to 10,000 Nigerian naira depending on the number of hours of participation. The conversion rate is 1 naira=US $0.00062).

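### The cost rule counts participant recruitment and participant compensation as intervention cost without separating research from delivery, and does not say that unit cost is reported by package

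*Protocol article*

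**What the plan says.** The Cost section under Aim 3 sets the scope: "Comprehensive records of all costs incurred in implementing the intervention will be kept". It then lists what is counted, "including the costs of recruiting the participants and other intervention implementation costs, such as facilitator and participant compensation", followed by training materials, equipment and venue, catering, transport and childcare. The output is stated in one sentence: "This will be used to calculate total costs as well as per-unit costs for participants".

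Ethical Considerations says what compensation pays for: "Participants will be compensated monetarily for their time participating in this study as well as their transportation costs". It gives the amount, "This compensation will range from 2000 Nigerian naira to 10,000 Nigerian naira depending on the number of hours of participation", and the exchange rate, "The conversion rate is 1 naira=US $0.00062".

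The Aim 3 Overview describes nested packages. For the first arm, "One of the intervention groups will receive the capacity building intervention package". For the next, "The second intervention group will receive the social protection intervention package in addition to the capacity building intervention package". A third arm serves as a control and gets neither package. Recruitment through social media, association meetings and partner organizations is described once, for the trial as a whole. Research Aims and the Aim 3 Overview both name the cost of the packages, in the plural, as one of the four things that the pilot assesses.

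**The concern.** Cost is a named aim, and the pilot is meant to inform scale-up and a larger trial. A policy maker needs to know what it costs per woman to deliver each package and what social protection adds. The costs of finding trial participants and paying them for surveys or interviews belong to the evaluation and would not recur in a programme.

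The Cost section places recruitment and participant compensation among the implementation costs and carries them into the unit cost. No section separates the research share from the delivery share. The section also refers to a single intervention where the design has two nested packages, and it names neither arm nor denominator. A reader of the eventual unit cost could not tell how much of it is delivery, or to which package it belongs.

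**Working it through.** **Figure to reproduce.** There is none. The article gives no cost total, unit cost or component cost.

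**Sections side by side.** The Cost section treats recruitment as one implementation cost among others and lists participant compensation with facilitator pay. Ethical Considerations ties compensation to hours in the study. The Overview recruits 150 women, 50 per arm, of whom one third get no package. (The Abstract says 300. The ratios below need only equal arms, so they do not depend on which total is right.) Recruitment and compensation therefore have a research component that the cost rule does not remove.

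**Size of compensation, from the article's figures.** 2000 × 0.00062 = US $1.24, and 10,000 × 0.00062 = US $6.20. The article does not say whether this is per contact. If it is (assumption), the five survey rounds (baseline, 6 weeks, months 4, 6 and 12) give 5 × 2000 = 10,000 to 5 × 10,000 = 50,000 naira per woman. At the stated rate that is US $6.20 to $31.00. The article also does not say that survey payments enter the cost total.

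**Effect on unit cost, costs split by arm.** Let D be delivery cost per woman and R the research cost per woman included with it. The reported figure is D + R, so the overstatement is R/D. All values here are assumed:

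- D = 100 and 200, R = 20: reported 120 and 220, overstated by 20/100 = 20% and 20/200 = 10%.
- D = 100 and 150, R = 10: reported 110 and 160, overstated by 10/100 = 10% and 10/150 = 6.7%.

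In both cases the difference between arms is unaffected (220 − 120 = 100; 160 − 110 = 50). If R is equal in the two arms, mixing distorts the level of each unit cost but not the incremental cost.

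**Recruitment of controls.** If recruitment for all three arms were divided over the treated women only (assumption), recruitment per treated woman would be 150/100 = 1.5 times its own-arm value.

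**Why the split by package matters.** If capacity building costs C per woman and social protection adds S, an average over two equal arms is C + S/2. The article does not say that it will average. This shows only what would follow if it did, with S/C assumed:

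| S/C | average ÷ C | error for capacity building | error for combined package |
|---|---|---|---|
| 0.25 | 1.125 | +12.5% | −10.0% |
| 0.5 | 1.25 | +25% | −16.7% |
| 1 | 1.5 | +50% | −25% |
| 2 | 2.0 | +100% | −33.3% |

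**The case against.** The strongest reply is that recruitment and compensation are not purely research costs. A programme at scale must also find and enrol women, and one recruitment partner is named in the Discussion as a partner for scale-up. The Cost section lists compensation beside venue, catering and childcare, so it may mean payment for attending sessions. Ethical Considerations covers the whole project and does not define the cost item. All of this stands. It means that each item has two parts, and the present rule cannot show how large each is. It does not answer the point that the parts are left mixed.

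A reader might infer more than the article supports:

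- That one pooled figure will be given for both packages. The article never says so. It speaks of per-unit costs and of packages in the plural, and silence on a split by arm is detail that an article may leave to a fuller document.
- That control-arm costs enter the total. The stated scope is implementing the intervention, which does not clearly include them.
- That neither package can get a sound unit cost. Comprehensive records are promised, and if itemised they could be separated at the reporting stage.

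**Conclusion.** The point holds in a limited form. The Cost section classes participant recruitment and participant compensation as implementation cost and feeds them into total and per-unit costs, with no separation of research from delivery. A unit cost computed literally would overstate delivery cost by R/D, where R is the research share per woman. Neither R nor D is given, so the size is unknown. The percentages above depend on assumed costs, and the US $6.20 to $31.00 depends on payment per survey contact. That the section does not say unit cost is reported by package is a secondary gap, worth closing because the stated aim is the cost of the packages. The primary outcome and the planned tests are not affected.

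**What to change.** Amend the Cost section so that each cost record carries two codes.

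- **Type.** Research-specific: trial recruitment, and compensation and travel for surveys or interviews. Delivery: facilitators, materials, venue, catering, childcare, transport to sessions, and any enrolment or attendance payment that would recur at roll-out.
- **Arm.** Capacity building, capacity building plus social protection, control, or shared.

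Report delivery cost per woman allocated, separately for the two packages, and give the difference as the incremental cost of social protection. Show research costs on a separate line outside the unit cost.

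This costs some wording and two codes on records that the plan already requires, with no new data from participants. The downside is that shared items, such as a facilitator or venue serving both arms, need an allocation rule, which should be written down before the costs are totalled. Delivery is under way and data collection runs to November 2025, so coding now is easier than reconstructing the split later.

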##### Outcomes

The primary outcome of this study is well-being (financial, mental, and physical). Financial well-being will be measured using the Consumer Financial Bureau Financial Well-Being Scale [45]. Mental and physical well-being will be measured using the 9-item Patient Health Questionnaire [46], the 12-item General Health Questionnaire [47], as well as the 12-item Short-Form Health Survey [48].

The secondary outcomes that will be measured are earnings, savings, perceived social support, as well as access to health care. Earnings will be measured by asking questions about participants’ revenues, costs, and profits from their sales. Savings will be measured by asking about the various persons, institutions, or organizations with which they save; how frequently they save; and how much they save each time they do. Social support will be measured using the Multidimensional Scale of Perceived Social Support [49] and the Self-Employment Social Support Scale [20].

In order to understand the pathways through which the interventions could affect the outcomes, questions will also be asked, which evaluate the knowledge, attitude, and practices of the self-employed young women who participate in the intervention in the various domains of the intervention, including business management; the use of digital technologies; the management of their personal and business finances; the use of resources available to self-employed young women in Oyo State; and caring for their mental, physical, and social health. Questions will also be asked to find out the number of business associations and other social groups that self-employed young women belong to, whether they have been rescued from any dire situations (eg, domestic violence), and how many of them are enrolled in health insurance. Questions will also be asked to members of the support network of self-employed young women who participate in the intervention to assess changes in their knowledge, attitudes, and practices toward providing support to the self-employed young women in their lives. Furthermore, the pre- and postintervention survey will include 3 rated items and an open-ended question about the impact of the last experienced significant life event on participants’ ability to meet their needs and on their well-being and work.

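### As worded, the knowledge, attitude and practice questions cover only women in the intervention and their support networks, which leaves those measures without an untreated comparison

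*Protocol article*

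**What the plan says.** The Outcomes section under Aim 3 lists the primary and secondary outcomes and then adds a further group of questions with its own purpose: "In order to understand the pathways through which the interventions could affect the outcomes". The first set evaluates the "knowledge, attitude, and practices of the self-employed young women who participate in the intervention in the various domains of the intervention", spanning business, digital, financial, resource-use and health topics. A later sentence directs similar questions to "members of the support network of self-employed young women who participate in the intervention to assess changes in their knowledge, attitudes, and practices" in how they give support.

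Between these two sentences come items on "the number of business associations and other social groups that self-employed young women belong to", on rescue from dire situations and on health insurance. They carry no such restriction. The life-event items at the end of the section refer simply to participants.

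On the arms, the Aim 3 Overview states: "The third group will be a control group serving as a comparison group, and participants will not receive any intervention". On the surveys it states: "All groups will participate in a preintervention survey". It adds: "Follow-up surveys will be conducted at 6 weeks at the end of the capacity building intervention and months 4, 6, and 12", without limiting these by arm. The Aim 3 Analysis section compares study outcomes across the three groups and compares each intervention group with control. It does not say whether the pathway measures count as study outcomes.

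**The concern.** KAP change is the most direct evidence on whether capacity building moved what it was meant to move. The Discussion says the pilot will be used to refine the packages before a large-scale efficacy trial, so these measures will help decide what is kept and what is changed.

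If only treated women are asked, a rise in KAP scores has several explanations that the data cannot tell apart:
- Up to five surveys are given over 12 months (baseline, 6 weeks, months 4, 6 and 12), and repeated questioning can itself change answers.
- The Background describes business support programmes for women already run by government and banks. One of them sits within an agency that is also a recruitment partner for the pilot.
- Business and economic conditions may shift over the year.

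The trial has a concurrent untreated arm that could account for trends common to all arms. The wording appears to leave it unused for these items.

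**Working it through.** This turns on wording, and the plan has no figure to reproduce. The relevant statements, side by side:

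| Item (Aim 3, Outcomes) | Who is named | Restricted to the intervention? |
|---|---|---|
| Earnings | participants | No |
| Women's KAP | women who take part in the intervention | Yes |
| Associations, rescue, insurance | self-employed young women | No |
| Support-network KAP | networks of women who take part in the intervention | Yes |
| Life-event items | participants | No |

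1. The section uses different terms for different items. The qualifier is attached to the two KAP sets and not to the other items in the table.
2. The Feasibility section uses a similar phrase for people asked, at the end of delivery, about scaling the intervention. There it most naturally means recipients.
3. The Overview gives the control arm no intervention. Taken together, the literal population of the KAP items is the two treated arms.
4. The Overview has all groups take the baseline survey and does not limit follow-up by arm. This shows that control women are available to answer. It does not show that every item is put to every arm.
5. If the wording is applied, two contrasts remain. The first is before versus after within a treated arm, which is open to the alternative explanations above. The second is capacity building versus capacity building plus social protection. That contrast is concurrent, but it informs only on the added component, because both arms receive capacity building.

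**Illustration only; the plan states no such test.** Suppose someone pooled the two treated arms and tested the mean KAP change at two-sided 5%. Inputs: the Overview's 120 participants before the attrition allowance give 120/3 = 40 per arm, so n = 2 × 40 = 80. The pre-post correlation r and a drift of d SD unrelated to the intervention are assumptions.

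SE = √(2(1−r)/n); probability of a significant result = P(Z > 1.96 − d/SE) + P(Z < −1.96 − d/SE).

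- r = 0.5, d = 0.2: SE = √(1/80) = 0.112, d/SE = 1.79, probability 0.432.
- d = 0.2 with r = 0.3 and 0.7: 0.327 and 0.637.
- d = 0.3 with r = 0.3, 0.5 and 0.7: 0.621, 0.765 and 0.934.

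This shows only that modest background drift can look like an effect when there is no control arm. It is not an error rate of this trial.

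**The case against.** The strongest reply is that the qualifier is loose wording for pilot participants. Nothing in the article expressly excludes controls, all groups take the baseline survey, follow-up is not limited by arm, and the third arm is described as a comparison group. A journal article also commonly leaves to the full protocol which questionnaire module goes to which arm. This stands in part: exclusion of controls is an inference from the wording and not a stated rule. But the article does name a population, twice, while describing neighbouring items differently. If controls were meant to be included, the sentence is at odds with the three-arm design and still needs correcting.

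A reader might infer three stronger things, none of which the document supports:
- **That the whole pathway assessment lacks a control.** The association, rescue, insurance and life-event items carry no restriction.
- **That the plan will read before-after change as mechanism.** The Analysis section plans no within-arm pre-post test and no mediation analysis; its stated approach is comparison between groups. Only the support-network sentence speaks of assessing changes.
- **That false-positive rates such as those in the illustration apply to this trial.** They belong to a pooled test that the plan does not state, with assumed drift and correlation.

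It is also fair to say that these are exploratory measures in a pilot whose main aims are feasibility, acceptability, cost and potential effectiveness.

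**Conclusion.** The point holds in a limited form. The KAP questions, for the women and for their support networks, are worded for intervention participants only, in a trial with a concurrent untreated arm that takes the surveys. Followed as written, KAP change would have no untreated comparison and could not be attributed to the packages. The support-network sentence matters most here, because it combines the restriction with an aim of assessing change.

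The reach is two sets of exploratory items. The primary and secondary outcomes and the unrestricted pathway items are not affected. The conclusion assumes that the questionnaires follow the published wording. If they already ask control women the same KAP items, only the text needs correcting for those items.

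**What to change.** In the Outcomes section, state that control women receive the same KAP items at every survey still to be done, and say whether they received them at baseline. In the Analysis section, state that KAP measures are compared between arms, adjusted for baseline where it is available. State also whether control women's support networks are surveyed. If network members are surveyed only in the intervention arms, or if control KAP data were not collected, report those results as uncontrolled within-arm change and not as an intervention effect. The association, rescue, insurance and life-event items need no change.

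The cost is a few extra survey minutes for about 50 control participants who are already surveyed. That number is the per-arm figure in the Aim 3 Overview; the Abstract's total of 300 would give 300/3 = 100 if the arms were equal. The support-network part needs only a change of wording. There is one limit: Table 3 in Results says the packages are already being delivered. If control women were not asked the KAP items at baseline, those data cannot be recovered and baseline adjustment will not be possible. The remaining follow-ups and the reporting can still be put right.
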